
## Statistical considerations

### Methods of data collection

Patient-level data (demographics, obstetrical history, and family history) will be collected at the time of digital acquisition of heart records, and stored (as previously indicated) in a customary, web-based, properly encrypted database with digital anonymization, by dedicated research personnel. Digital acquisition of heart records will be acquired as previously specified. Echocardiography will be performed by dedicated experienced paediatric cardiovascular imagers. A preliminary inter- and intra-observer variability for the echocardiographic evaluation will be run on 1% of total population (variability testing cohort).

### Statistic plan

Between-group comparisons for clinical and outcome variables will be performed using independent samples *t*-test, Wilcoxon rank sum test, chi-square analysis, or Fisher's exact test using appropriate variable-specific denominators.

For experimental design Aim 1, limited data are available to build up a reliable power calculation at this stage, but we expect to enrol 600 patients with 2:1 diseased:healthy newborn ratio in this experimental phase. The rationale behind the ratio is due to the higher variability of diseased subjects with respect to the healthy ones.

Specific potential classifiers will be studied in the spectral features, cepstral features, and time-domain features. Dataset will be split into training set, validation set, and test data set. The performance of the classifiers will be evaluated using K-Fold cross-validation. Different folding levels will be tested: 10-fold, 5-fold, and LOOCV, aiming for >95% sensitivity and >90% specificity. The numerosity of the sample we target will allow to estimate the target sensitivity and specificity with sufficient accuracy, in particular with the target numerosity we can estimate a 95% confidence interval of ±2% in the sensitivity estimate and ±4% for the specificity estimate.

Gini importance for Random Forest classifiers will be used as a tool to validate parameters with least predictive contribution. Gini importance can be defined as the probability of making a false classification of a randomly chosen record if it were randomly labelled in the class distribution. During the training of the decision trees of the random forest, each tree is a set of internal nodes and leaves. In the internal node, selected feature is used to make decision of dividing the dataset into two separate splits. Selection of the feature is done with Gini impurity criterion. The feature that brings the highest decrease of Gini impurity is selected for the internal nodes. Even after training, how each feature decreases the impurity can be calculated and accepted as the importance of that feature.

Net classification improvement will be used as the major statistical analysis for Experimental Aim 2, using ‘standard of care’ screening modality as comparison group. Sensitivity, specificity, positive, and negative predictive values will be calculated, and likelihood ratio will be analysed. C-statistics will be used to compute diagnostic performance of newly validated algorithm. Bootstrapping will be used to generate confidence intervals.

For experimental design Aim 2, sample size calculation is being presented for sensitivity. Assuming a two-sided α of 0.05% and 90% power, and a disease prevalence of 1% consistent with prior newborn CHD screening studies, we based our calculation on methods for diagnostic test evaluation. Specifically, targeting a sensitivity of approximately 90% with a desired confidence interval width of ±10%, at least 19–20 cases of CHD are required. Given the low expected prevalence (1%), this corresponds to a total sample size of approximately 1900–2000 newborns. This approach is consistent with previously published recommendations for validation of diagnostic algorithms in low-prevalence settings.^34^ Accordingly, an independent validation cohort of approximately 1900 consecutively enrolled participants will be used.

Data will be reported as mean ± standard deviation, median (first and third quartile) or frequency (%). All tests were two-sided. A *P*-value <0.05 was considered significant. Standard statistical analysis will be performed using STATA® 17 h Release data analysis software (StataCorp LP, College Station, TX).

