Phonocardiographic signals will be stored as wav files in an encrypted cloud system to be transferred for further analysis (*Graphical abstract*). Tracings will undergo preliminary processing to remove background noise, and will be segmented to generate sound samples of homogeneous suitable tuned duration. As the last step of the preprocessing, the filtered records will be normalized for preventing inhomogeneity in the extracted features. Data analysis will be then implemented based on handcrafted feature extraction. The main objective of feature extraction is to identify a small number of representative features characteristic properties of a sound sample, that replace the high-dimensional raw signals still preserving its informative content with respect to the phenomenon under investigation. Relevant features are then fed to the classification algorithm to discriminate between healthy and abnormal subjects. Multiple different techniques will be used for feature extraction in sound signals, and can be loosely grouped into frequency-domain techniques, time-frequency domain techniques, linear predictive coding, and time-domain techniques. Each of these techniques provides descriptors of potentially relevant properties of the sound sample, which can be used as features or further processed to extract higher level characteristics of the signal (such as systole and diastole variability). To maximize the robustness of our results to less-than-ideal acquisition conditions, we will train the classifiers using features from all the above-mentioned domains and will perform a feature selection procedure to select those features which are mostly correlated to the outcome of interest. Standard machine learning models will be preferred, as simpler models tend to perform more robustly when training data is limited. Neural networks may be implemented if they will exhibit superior results with respect to standard models on the available dataset without clear signs of overfitting. Following the standard best practice, the dataset will be split into training set, validation set and test data set. For evaluating the performance of classifiers, K-Fold cross-validation with different fold numbers will be used: 10-fold, 5-fold, and Leave-One-Out-Cross-Validation (LOOCV). In LOOCV, the number of folds is equal to number of records. Gini importance for Random Forest classifiers will be used as a tool to validate parameters with least predictive contribution. Once a proper classifier has been trained a post training analysis to determine the most relevant features will be conducted. The purpose of this analysis is to investigate to which extent each feature is contributing to the selection of one class with respect to the other. Techniques for feature relevance estimation based on SHAP values, or permutation analysis will be applied also with the aim of providing a proper explanation to the model decision (*Graphical abstract*).

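### Aim 1 selects features and model on the same 600 newborns whose cross-validated results are set against the performance aim, so the reported sensitivity and specificity will be somewhat optimistic

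*Protocol article*

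**What the plan says.** All of this is in the protocol article.

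- **Sample (Statistic plan, Aim 1).** "we expect to enrol 600 patients with 2:1 diseased:healthy newborn ratio in this experimental phase", that is, 400 with and 200 without structural heart disease (SHD).
- **Evaluation (Statistic plan).** "The performance of the classifiers will be evaluated using K-Fold cross-validation". The performance aim is tied to that method: "Different folding levels will be tested: 10-fold, 5-fold, and LOOCV, aiming for >95% sensitivity and >90% specificity".
- **Precision (Statistic plan).** With this sample, "we can estimate a 95% confidence interval of ±2% in the sensitivity estimate and ±4% for the specificity estimate".
- **Model choice (Study procedure, Derivation phase).** Standard machine learning models are preferred, but "Neural networks may be implemented if they will exhibit superior results with respect to standard models on the available dataset without clear signs of overfitting".
- **Feature choice (Derivation phase).** Features from several domains are computed, and those most correlated with the outcome are kept. The section does not say that this happens separately within each training fold.
- **Split (Derivation phase, repeated in the Statistic plan).** "the dataset will be split into training set, validation set and test data set". Neither section gives the size of the test set or ties the performance aim to it.
- **Records (Derivation phase).** Three recordings per newborn are anticipated, tracings are cut into segments, and leave-one-out cross-validation (LOOCV) is defined with as many folds as records.

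**The concern.** A cross-validated estimate is close to unbiased for a procedure fixed in advance. It is no longer so once the same results, or the same outcome data outside the folds, have been used to choose features, model family or threshold. The winner is partly the candidate that was lucky in these 600 newborns, and its reported performance carries that luck. An untouched test set would remove the problem, but the plan does not say that the test set supplies the Aim 1 figure, and its own precision statement implies otherwise.

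At stake is the published Aim 1 sensitivity and specificity. The ±2% and ±4% describe sampling error for a fixed classifier. They make no allowance for selection, so the intervals would be centred too high. Aim 2 plans its sensitivity to ±10% on 19–20 cases. Unless the high-risk stratum adds many more cases, the Aim 1 figure would look like the study's most precise statement on sensitivity.

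**Working it through.** **1. Reproduce the stated precision.** Inputs: sensitivity 0.95 with n = 400 and specificity 0.90 with n = 200, from the aim and the 2:1 ratio in 600. Wald half-width = 1.96 × √(p(1 − p)/n).

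- Sensitivity: 1.96 × √(0.95 × 0.05/400) = 0.0214, or ±2.14 points.
- Specificity: 1.96 × √(0.90 × 0.10/200) = 0.0416, or ±4.16 points.

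Both round to the stated ±2% and ±4%. The precision statement therefore uses every newborn as an evaluation case.

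**2. What a held-out test set would give.** The article states no split, so the share is an assumption.

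| Test share (assumed) | SHD / healthy | Sensitivity | Specificity |
|---|---|---|---|
| 10% | 40 / 20 | ±6.8 | ±13.1 |
| 20% | 80 / 40 | ±4.8 | ±9.3 |
| 30% | 120 / 60 | ±3.9 | ±7.6 |

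None of these shares reaches the stated figures.

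**3. Optimism from choosing among equally good candidates.** Assumptions: ten candidates, all truly at 94% sensitivity and 89% specificity; the best by sensitivity plus specificity is chosen; correlation ρ between candidates is 0.5 or 0.8.

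- Standard errors: √(0.94 × 0.06/400) = 1.19 points and √(0.89 × 0.11/200) = 2.21 points. For the sum: √(1.19² + 2.21²) = 2.51 points.
- The expected maximum of ten independent standard normals is 1.54, so the mean excess of the winner's sum is 1.54 × 2.51 × √(1 − ρ): 2.7 points at ρ = 0.5 and 1.7 at ρ = 0.8.
- Sensitivity takes the share 1.19²/2.51² = 0.22 and specificity takes 0.78. This gives 0.6 and 2.1 points at ρ = 0.5, and 0.4 and 1.3 points at ρ = 0.8.

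**4. A simulation with real cross-validation.** Six linear classifiers were each run under 5-fold, 10-fold and LOOCV on 600 simulated newborns (18 results per run, 300 runs). Taking the best of the 18 gave mean optimism of 0.3 points in sensitivity and 0.6 in specificity. One feature set was clearly better there, which lowers the figure.

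**5. Where the optimism comes from.** In that simulation the three fold schemes for one classifier correlated 0.76 to 0.88, and different classifiers about 0.34. Re-running one classifier under three schemes therefore adds little; choosing among classifiers adds most. Selecting features on outcome outside the folds would add further optimism, which was not quantified.

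**6. Chance of crossing both point targets when the truth is below them.** Assume a true 94% and 88%. For one look, P(sensitivity estimate > 0.95) = P(Z > 0.01/0.0119) = 0.200 and P(specificity estimate > 0.90) = P(Z > 0.02/0.0230) = 0.192; the product is 3.8%. For the best of 15 looks, simulation gives 16% (ρ = 0.8) to 27% (ρ = 0.5). This illustrates direction only, since the number of looks is assumed.

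**The case against.** - **Aim 2 already supplies independent validation.** About 1,900 consecutively enrolled newborns, with echocardiography as reference, will test the classifier. This stands: Aim 1 optimism does not bias Aim 2, and the harm is confined to the Aim 1 figure.
- **The plan has safeguards.** It prefers simpler models, and neural networks are conditional on no clear sign of overfitting. This partly stands. These limit overfitting but do not correct the estimate for selection.
- **The article condenses a fuller protocol.** Test-set size and nesting may be set out there. If features are in fact selected inside the folds, the optimism from that source disappears. But the article fixes cross-validation as the evaluation, and its precision statement needs all 600 newborns. That is a stated choice that does not fit with a held-out test set, and not only missing detail.
- **The size is assumed.** This stands. The candidates, their correlation and their true performance are not in the article, and equally good candidates favour large optimism. Even the larger values lie within the stated ±2% and ±4%.
- **A stronger inference.** A reader might infer that success can be declared by reporting the best of many classifier and fold-scheme combinations. The text does not support this. The figures are worded as an aim, Aim 2 is not made conditional on them, and nothing says that the most favourable scheme will be selected or reported. That cross-validation picks the winner is itself a reading of the two sections together, although it is the only evaluation of the classifiers described for Aim 1.

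**Conclusion.** The point holds in limited form. As written, features and model family are chosen on the same 600 newborns whose cross-validated results are set against the >95% and >90% aim, and the announced test split cannot be the source of the stated ±2% and ±4%. The Aim 1 performance of the chosen classifier will be somewhat optimistic: from about 0.3 points in sensitivity and 0.6 in specificity, where one feature set was clearly better, to about 0.6 and 2.1 points with ten equally good candidates at correlation 0.5. These sizes rest on assumed candidates and exclude any leakage from feature selection. The three fold schemes are a minor source.

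**What to change.** In the Aim 1 part of the Statistic plan, name one nested cross-validation as the Aim 1 performance estimate:

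- Assign folds by newborn, so that all recordings and segments from one infant stay together. LOOCV with one fold per record might otherwise leave the same infant's other recordings in training.
- Carry out feature, model and threshold selection only in the inner folds.
- Compare the outer-fold sensitivity and specificity, once, with the >95% and >90% aim. All 600 newborns serve as test cases, so the ±2% and ±4% remain approximately right.
- Report 5-fold and LOOCV results as sensitivity analyses.

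If a held-out test set is preferred, state its size, keep it out of all selection and restate the precision, for example about ±4.8 and ±9.3 points with an assumed 20% share.

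The nested option costs computing time and a few sentences, and the reported performance will look slightly less favourable. Enrolment and procedures are unchanged. The test-set option also gives up much of the stated precision.

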## Limitation

The most notable limitation is the absence of reliable data to calculate power for the development/training phase. Second, some severe SHD (among others transposition of the great arteries with intact ventricular septum) may have minimal acoustic correlates, and, therefore, our approach may be of limited efficiency for these lesions. Third, clinical screening modality integrates a variety of non-acoustic information, such as general newborn appearance, breathing pattern, femoral pulses, oxygen saturation. It is possible that clinical screening method may outperform digital screening for specific subsets of congenital lesions. Fourth, the frequency response of the digital stethoscope may change significantly between stethoscope models, and this may affect the ability of the classifier to transfer performance to a different model. To mitigate this aspect, we have decided to disable all digital filtering and equalization upon sound acquisition. Development and validation of diagnostic tool in a specific world region may constitute *per se* a limit affecting world-wide generalizability. Lastly, small/premature neonates (<1.5 kg) were not included in the target population of our study by design. This neonatal population routinely undergoes comprehensive cardiovascular evaluation, including echocardiographic screening, which reduces the potential added value of a digital heart sound–based screening tool in this subgroup. They frequently present with clinical and physiological conditions (such as mechanical ventilation, underlying lung disease, haemodynamically significant patent ductus arteriosus, and pulmonary vascular abnormalities) that may introduce substantial acoustic variability and confound heart sound recordings. These factors would limit both the reliability of data acquisition and the generalizability of a classifier intended for the broader neonatal population. Fifth, we are aware that a specificity of 90% may be considered lower than expected for a screening test, however, few consideration should be made to this regard: (i) specificity for current clinical screening modality is reported to be between 95% and 99% with a much lower sensitivity (70–80%) and (ii) our boundary condition is assumed under worst case scenario but we aim for a significantly higher specificity and in the Supplementary material online, *Table S3* of the Online Supplementary Material we are reporting a summary table for diagnostic performance of our classifier under different scenarios showing a sustainable workload for lower specificity compared with optimal specificity (about 80 false-positive newborns every/1000). Finally, given the clinical fragility of preterm infants, we carefully considered the ethical implications of additional handling and sensor application and examination, including potential risks of infection and discomfort.

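### The sample size for Aim 2 covers the precision of one sensitivity, so its 90% power belongs to no hypothesis and the major comparison with clinical screening has no power statement

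*Protocol article*

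**What the plan says.** All of the Aim 2 planning is in the Protocol article, Statistic plan.

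- **Major analysis:** "Net classification improvement will be used as the major statistical analysis for Experimental Aim 2", against standard-of-care screening. The article gives no formula, weights or components. Sensitivity, specificity, predictive values, likelihood ratios and a C-statistic are also planned, with bootstrap intervals.
- **Basis of the sample size:** "sample size calculation is being presented for sensitivity". The calculation opens with "Assuming a two-sided α of 0.05% and 90% power, and a disease prevalence of 1" per cent, and continues: "targeting a sensitivity of approximately 90% with a desired confidence interval width of ±10%, at least 19–20 cases of CHD are required". The result is that "an independent validation cohort of approximately 1900 consecutively enrolled participants will be used".
- **Significance level for tests,** later in the same section: a P-"value <0.05 was considered significant", two-sided.
- **Performance target of the classifier,** stated under Aim 1: "aiming for >95% sensitivity and >90% specificity".

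For the comparator, the Limitation section says "specificity for current clinical screening modality is reported to be between 95% and 99% with a much lower sensitivity (70–80" per cent). It calls 90% specificity for the classifier a worst-case boundary and hopes for clearly better.

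**The concern.** The quantity used to size the study is not the quantity named as the main result. A precision calculation for one proportion needs an expected value, a half-width and a confidence level. It has no null value, no alternative and no second test, so power has nothing to act on. A reader who sees 90% power beside a comparative major analysis will assume that the comparison is well powered, and nothing in the article supports that.

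The choice of measure adds a second weakness. For two binary tests, the usual net improvement is the difference in sensitivity plus the difference in specificity. At 1% prevalence the first term rests on about 19 newborns and the second on about 1,881, yet a percentage point counts the same in each. The sum can therefore be positive when the digital test gains a few detections at the price of many more false positives. The Discussion asks for a tool that improves both sensitivity and specificity, and a positive sum cannot show that both improved.

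**Working it through.** **Inputs from the article.** 1900 newborns at 1% prevalence give 19 cases and 1,881 non-cases. Digital sensitivity is 90% (Aim 2 sample size) or 95% (Aim 1 target). Digital specificity is 90% (Aim 1 target). Clinical sensitivity is 70–80% and specificity 95–99%, with mid-points 75% and 97%.

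**Assumptions.** The article does not give the agreement between the two tests, so the range runs from independence given disease status to maximal agreement. Digital specificities of 95% and 97% are added because the article hopes for more than 90%.

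**1. The plan's own figure.** Cases = z²·Se(1 − Se)/d².

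- Se 90%, d = 0.10, two-sided 5%: 1.96² × 0.09/0.01 = 34.6, so 35 cases.
- The same with α = 0.05% as printed (z = 3.48): about 109 cases.
- Se 95%, two-sided 5%: 1.96² × 0.0475/0.01 = 18.2, so 19 cases.

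The printed 19–20 cases therefore match neither the printed α nor the printed 90% sensitivity. Power appears nowhere in the formula. Below, 19 cases is kept because it is the planned number.

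**2. Net improvement, one case worked by hand.** Digital 95%/90%, clinical 75%/97%, independence.

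- Sum: (0.95 − 0.75) + (0.90 − 0.97) = 0.20 − 0.07 = +0.13.
- Cases: the discordant proportions are 0.95 × 0.25 = 0.2375 and 0.05 × 0.75 = 0.0375, total 0.275. Variance = (0.275 − 0.20²)/19 = 0.01237.
- Non-cases: the discordant proportions are 0.90 × 0.03 = 0.027 and 0.10 × 0.97 = 0.097, total 0.124. Variance = (0.124 − 0.07²)/1,881 = 0.00006.
- Standard error = √0.01243 = 0.111, and 0.13/0.111 = 1.17.
- Power ≈ Φ(1.17 − 1.96) ≈ 21%; simulation gives 20%. About 99% of the variance comes from the 19 cases.

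**3. Range of power with 19 cases, clinical screening at 75%/97%, two-sided 5%.**

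| Comparison | Power |
|---|---|
| Net improvement, digital Sp 90%, Se 90% | 7–10% |
| Net improvement, digital Sp 90%, Se 95% | 19–20% |
| Net improvement, digital Sp 95–97%, Se 90–95% | about 22–54% |
| Paired sensitivity, exact McNemar, Se 90–95% | about 5–17% |
| Paired sensitivity, asymptotic McNemar, Se 90–95% | up to about 54% |

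The most favourable setting tried was digital sensitivity 95% against 70%, equal specificities and maximal agreement. It gave 74% for the net improvement.

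**4. Cases needed for 90% power** at 75%/97% and digital specificity 90%, with 99 non-cases per case. The formula is n = (1.96 + 1.28)² × V/(net improvement)², where V is the case variance plus 1/99 of the non-case variance, each per newborn.

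- Se 95%, independence: V = 0.235 + 0.1191/99 = 0.2362, and 10.51 × 0.2362/0.13² ≈ 147 cases. Maximal agreement gives 100.
- Se 90% (net improvement +0.08): 211 to 458 cases.

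**5. False positives per 1,000 newborns at 1% prevalence** (digital 95%/90%, clinical 75%/97%).

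- Extra detections: 10 × 0.20 = 2.
- Extra false positives: 990 × 0.07 ≈ 69 (about 30 rising to 99).

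Across comparator specificities of 95–99%, the sum stays positive (+0.20 − 0.05 = +0.15 down to +0.20 − 0.09 = +0.11). False positives among 1,881 non-cases rise from 94 or 19 to 188, a factor of 2 to 10.

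**The case against.** Several points on the other side stand and limit what can be said.

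- **Power for the net improvement.** A reader might infer that the article claims 90% power for it. It does not: the sentence belongs to the sensitivity calculation. The defect is that the power has no hypothesis there and that the major comparison has no power statement.
- **Hidden trade-off.** A reader might infer that false positives are concealed. They are not. Sensitivity, specificity and predictive values are planned, false positives and false negatives are defined for each screen, Aim 3 counts unnecessary and missed examinations, and the Limitation section discusses the lower specificity openly. The weakness is in the choice of headline measure.
- **Formula not given.** A condensed article may leave the definition to another document. The false-positive argument applies only to the unweighted sum; a prevalence-weighted or by-component version would avoid it.
- **Worst-case specificity.** The +69 false positives use what the article calls its worst case. With specificity equal to clinical screening they would not rise, though power at 19 cases would still be below 90%.
- **Role of α.** It does enter an interval-based sample size, through z. Only the power is idle.
- **More cases than 19.** Validation enrolment is stratified into high- and low-risk newborns, with no ratio given. With 100 cases in 1900, power for the net improvement at digital specificity 90% under independence is about 33% (Se 90%) or 77% (Se 95%); with 200 cases, about 56% or 96%. Closer agreement can raise these. The article's own calculation nevertheless uses 1% prevalence.

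**Conclusion.** The point holds in this form. The 90% power is attached to no hypothesis, the major Aim 2 comparison is unsized, and α of 0.05% contradicts the 0.05 level in the same section. These follow from the text alone and need no assumption.

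The size of the shortfall rests on 19 cases, the mid-points of the comparator ranges, and an unstated agreement between the tests. Within those limits, no version of the comparison with clinical screening comes near 90%. No single power figure is safe to quote, because the result moves with specificity, agreement and the version of the test. A well-enriched cohort could change the picture.

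The statement that the headline can be positive while false positives multiply is conditional on the unweighted sum and on a digital specificity below that of clinical screening.

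**What to change.** 1. State α = 0.05, two-sided, in the Aim 2 sample-size paragraph.
2. Delete the 90% power claim, or replace it with power computed for the comparison actually made. Give the assumed performance of both tests, their agreement, the expected number of cases (including any from the high-risk block) and the resulting range.
3. Make two paired differences the headline Aim 2 result: sensitivity in newborns with SHD and specificity in newborns without SHD, each with a paired 95% confidence interval.
4. Keep the net improvement as a secondary measure, shown by event and non-event component or weighted by prevalence, with its formula.

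Each newborn already has both screens and an echocardiogram, so no new data are needed. The cost is wording and a few lines of analysis. The price is that the stated power becomes less favourable.

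### Aim 2: bootstrap confidence intervals for sensitivity fall well short of 95% coverage at the planned 19–20 cases if true sensitivity is 90–95%, and collapse to 100–100% if no case is missed

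*Protocol article*

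**What the plan says.** In the Protocol article, the Aim 2 part of the Statistic plan names net classification improvement against standard screening as the major analysis. It then states "Sensitivity, specificity, positive, and negative predictive values will be calculated, and likelihood ratio will be analysed", adds the C-statistic, and closes the list with "Bootstrapping will be used to generate confidence intervals". That sentence is not limited to one measure, and the article gives no other interval method for Aim 2.

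The next paragraph sizes Aim 2 on sensitivity: "targeting a sensitivity of approximately 90% with a desired confidence interval width of ±10%, at least 19–20 cases of CHD are required". It continues: "Given the low expected prevalence (1%), this corresponds to a total sample size of approximately 1900–2000 newborns". The cohort is then set at about 1900.

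Two further places matter. For Aim 1, the same section describes the classifier as "aiming for >95% sensitivity and >90% specificity". The validation-phase sections describe enrolment stratified into high-risk and low-risk newborns, without giving the proportions.

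**The concern.** A bootstrap of a proportion can only reshuffle the detections and misses that were observed. With about 20 cases and a sensitivity near 90–95%, the expected number of misses is one or two, and it may be zero. With zero misses every resample has a sensitivity of 100%, so the interval has no width. The negative predictive value becomes 100–100% and the negative likelihood ratio 0–0 in the same way. With one miss, the lower limit is still too high.

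Sensitivity is the quantity Aim 2 is sized on, and the Discussion treats false negatives as a significant clinical risk. The study could report perfect sensitivity with no apparent uncertainty from 19 affected newborns, when the data would still be compatible with a true sensitivity of about 82%. In these settings the fault makes the classifier look better established than it is.

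**Working it through.** **Inputs.** From the Statistic plan: planning sensitivity 0.90 with ±0.10 (Aim 2), prevalence 1%, about 1900–2000 newborns, hence 19–20 cases; target sensitivity above 0.95 (Aim 1), taken here as 0.95. Assumption: reported intervals are two-sided 95%. The text prints "Assuming a two-sided α of 0.05% and 90% power", but elsewhere uses a significance level of 0.05.

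**The plan's own case count.** The usual precision formula is n = z²·p(1−p)/d².
- p = 0.90, d = 0.10: 1.96² × 0.09 / 0.01 = 34.6, so 35 cases, or 3500 newborns at 1%. This does not give 19–20.
- p = 0.95, d = 0.10: 1.96² × 0.0475 / 0.01 = 18.2, so 19 cases, or 1900 newborns. This matches the printed total.

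The printed count therefore does not follow from the printed sensitivity by this formula. That is a separate matter. Below, 19–20 is taken as the plan states it.

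**Exact coverage of the percentile bootstrap.** If x of n cases are detected, the resampled number of detections is Binomial(n, x/n). The interval runs between its 2.5% and 97.5% quantiles, divided by n. Coverage is the sum of Binomial(n, p) probabilities over those x whose interval contains p. A limit that falls exactly on p is counted as covering, which favours the bootstrap.

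For n = 19, p = 0.90:

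| Misses | Probability | Bootstrap interval | Contains 0.90? |
|---|---|---|---|
| 0 | 0.135 | 1.000–1.000 | no |
| 1 | 0.285 | 0.842–1.000 | yes |
| 2 | 0.285 | 0.737–1.000 | yes |
| 3 | 0.180 | 0.684–1.000 | yes |
| 4 | 0.080 | 0.579–0.947 | yes |
| 5 | 0.027 | 0.526–0.895 | no |

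Coverage = 0.285 + 0.285 + 0.180 + 0.080 = 0.830. More than five misses also fails to cover and has a probability below 0.01.

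The same sum for the other settings, with the standard alternatives:

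| Cases | True sensitivity | Percentile bootstrap | Wilson | Clopper-Pearson | Chance of no misses (pⁿ) |
|---|---|---|---|---|---|
| 19 | 0.90 | 83.0% | 96.5% | 99.1% | 13.5% |
| 20 | 0.90 | 87.6% | 95.7% | 98.9% | 12.2% |
| 19 | 0.95 | 60.9% | 93.3% | 98.7% | 37.7% |
| 20 | 0.95 | 63.9% | 92.5% | 98.4% | 35.8% |

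**Does the choice of bootstrap matter?** Normal-based and BCa versions give 83–88% at 0.90 and 56–64% at 0.95. Resampling the whole cohort of 1900 or 2000 with a random number of cases gives about 85–86% and 60–63%. No common variant removes the shortfall.

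**Single results on 19 cases.**
- 19 of 19 detected: bootstrap 100–100%; Wilson 83.2–100%; Clopper-Pearson 82.4–100% (lower limit 0.025^(1/19) = 0.824).
- 18 of 19 detected: lower limit 84.2% by bootstrap, 75.4% by Wilson, 74.0% by Clopper-Pearson.

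**Where the problem fades.**
- True sensitivity 0.80–0.85 with 19–20 cases: percentile coverage 89–96%.
- 35 cases: 87.1% at 0.90 and 82.7% at 0.95, still short.
- An assumed 5% prevalence among 1900 newborns (about 95 cases): about 95% at 0.90 and 93% at 0.95.

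**The case against.** The strongest reply is textual. The bootstrap sentence directly follows the one on the C-statistic, in a paragraph led by net classification improvement, and bootstrapping is a usual choice for both. Applying it to sensitivity is an inference. It remains the natural one: the sentence speaks of confidence intervals in general and closes the list of all the measures. If the narrower meaning was intended, the same one-sentence change makes that clear. That the article names no bootstrap variant is not itself a fault, since such detail may sit in the full protocol or analysis plan.

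Second, the case count is a floor: "at least 19–20 cases of CHD are required". The high-risk stratum includes newborns with a suspicious foetal ultrasound or an abnormal screen, and could raise the number of cases well above 1%. This stands. At about 95 cases there is little left to correct. But the stratum proportions are not given, the sample size is worked at 1%, and the low-risk subset used for Aim 3 would not be enriched.

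Third, the worst figures use the Aim 1 target. At the Aim 2 planning value the shortfall is roughly 7 to 12 points. If true sensitivity is nearer 80–85%, it is small or absent. The Limitation section concedes that some severe lesions may have minimal acoustic correlates, so lower values are possible. This stands as a condition on the finding.

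Fourth, no success criterion in the article depends on the lower limit, and an exact interval can be computed from the two-by-two table at any time. This limits the consequence but does not make the stated method suitable.

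A reader might also infer that the plan contradicts itself by sizing with a binomial precision formula and reporting bootstrap intervals. The documents do not support that. The article refers only to methods for diagnostic test evaluation, and using one formula for planning and another interval for reporting is not an error in itself.

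**Conclusion.** The concern holds conditionally. At 19–20 cases, a nominal 95% percentile bootstrap interval for sensitivity has actual coverage of about 83–88% if true sensitivity is 90% and about 61–64% if it is 95%. The chance of a zero-width interval at 100% is 12–14% and 36–38% respectively.

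This rests on three assumptions: that the bootstrap sentence applies to sensitivity, that the case count stays near the stated minimum, and that true sensitivity is at the protocol's own planning or target value. A reader might infer that the reported intervals will be badly wrong whatever happens. The documents do not support that, because coverage is close to nominal near 80–85% sensitivity or with roughly 95 or more cases.

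Point estimates, data collection and design are unaffected. The change is worth making because the fault would fall on the key safety estimate in the very situation where the classifier performs as hoped.

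**What to change.** Replace the bootstrap sentence with wording to this effect: two-sided 95% confidence intervals for sensitivity, specificity and predictive values will use the Wilson score (or Clopper-Pearson) method; the negative likelihood ratio will use a score-type interval that remains valid with zero false negatives; bootstrapping will be used for net classification improvement and the C-statistic. The bootstrap should not be confined to the C-statistic, since that would leave the declared major Aim 2 analysis without a stated interval method. The planned precision for sensitivity should be stated with the same interval method that will be reported.

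The cost is one sentence and standard methods, with no extra newborns or data. The intervals for sensitivity will be wider, and Clopper-Pearson is somewhat conservative (98–99% coverage at these settings, against 92.5–96.5% for Wilson).
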